
### Participant selection and recruitment

Study participants include VA employees who are involved in the monitoring and management of patients treated with antipsychotics at participating sites and who completed surveys and interviews about related practices and quality improvement efforts; and VA patients prescribed antipsychotic medications, whose administrative and medical record data are obtained and analyzed to assess metabolic monitoring and management rates throughout the study. Employee participants were recruited solely by the research team to ensure confidentiality and avoid coercion. The study was reviewed and approved by the VA Central IRB and the Central Arkansas Veterans Healthcare System Research & Development Committee.

### EBQI/F intervention

Promoting Action on Research Implementation in Health Services (PARIHS) is the conceptual framework that guides and informs our intervention and evaluation approaches for this study. In this framework, successful implementation (SI) is represented as a function (f) of the nature and type of evidence (E), the qualities of the context (C) in which the evidence is being introduced, and the way the process is facilitated (F): SI = f(E, C, F) [36]. ‘Evidence’ includes knowledge obtained through research, clinician experiences, performance feedback, patient preferences, and other sources. ‘Context’ includes factors that may affect implementation of evidence-based practices, such as organizational culture/climate, readiness-to-change, leadership quality, resources, and the organization’s approach to evaluation. ‘Facilitation’ of the intervention by external and/or internal change agents can also affect implementation success [36,37].

The EBQI/F intervention, which involves researchers partnering with clinical stakeholders, is designed in a manner that is consistent with available research evidence and reflects the knowledge and expertise of site participants regarding how to tailor the strategy to local needs, priorities and resources. The intervention combines: EBQI processes in the EBQI Design Phase to design and tailor the initial implementation strategy to the local context, and external facilitation to support, monitor, problem-solve and refine implementation (as needed) during the study’s Implementation Phase. Further, through combining strategies and tools included in the MIAMI Project (see above) with EBQI and facilitation, the EBQI/F intervention provides a multifaceted approach to improving care in this area [38-41].

For the current project, the automated computer routine that was developed during the ASSIST Project (see above) was revised to identify patients who had been prescribed a new antipsychotic medication and were due for baseline or initial follow-up monitoring. Reports generated by this routine list weight, BMI, and relevant laboratory test results, if these tests were done. Additional computer routines were developed to generate a list of patients with abnormal laboratory results, and indicate whether management actions had been taken (*e.g*., prescription of a hypoglycemic agent following an elevated glucose test). The research team obtained approval from the VA Office of Information & Technology to install this software at study sites.

### EBQI design phase

The EBQI Design Phase includes an initial site visit and subsequent development of a local implementation plan at each site. In this phase, researchers contribute knowledge about the evidence base for clinical care and implementation strategies, providing implementation tools and materials. Clinical stakeholders contribute local knowledge and expertise needed to tailor implementation tools/strategies to match organizational needs, priorities and capabilities.

EBQI participants at each intervention site include approximately two to four key staff (*i.e*., administrative leaders, clinicians, nurses) involved in monitoring and managing patients treated with antipsychotics who were identified based on discussions between the study PI and site mental health leaders.

The EBQI Design Phase includes consideration of site-specific data collected in the developmental formative evaluation (see below), such as current practices, barriers/facilitators, key issues, and potential solutions in addressing project goals. These data were gathered through qualitative interviews conducted prior to the start of implementation activities, analyzed using a rapid analysis approach [42,43], and shared with EBQI participants to assist in development of local implementation strategies. In addition, EBQI participants were provided local performance data on metabolic monitoring and management, extracted from VA databases as described below for a six-month period prior to the site visit.

During the EBQI Design Phase, EBQI participants consider the QI tools/resources included in the MIAMI Project as well as additional monitoring and management tools and strategies that may be useful for local implementation. The duration of the EBQI Design Phase varies across sites, an understandable phenomenon in implementation studies, where preparation, design and implementation are often classified as distinct phases and differ depending on activities at each intervention site [44].

### Implementation phase: active facilitation

The Implementation Phase of this study is guided by an experienced and well-respected researcher ([name]), who serves as the lead facilitator, and a co-facilitator. Facilitator roles are to establish and leverage relationships with clinical stakeholders in order to encourage, support and guide them in executing the local implementation strategy.

It is expected that specific facilitation activities will vary by site because the context/needs of individual sites will also vary, while the roles of the facilitator will remain consistent with key components of external facilitation—including interactive problem-solving and support—as identified in our earlier MH QUERI research [37]. A time/activity log maintained by the facilitator will document all facilitation activities. This log will be used to estimate costs of the EBQI/F intervention as described in Data Analysis.

### Evaluation

Evaluation will include formative and summative evaluation activities. Formative evaluation (FE) is designed to identify potential and actual influences on the progress and effectiveness of implementation efforts. It also helps optimize the potential for success by providing a better understanding of the processes involved, identifying and addressing needed refinements to the implementation strategy, and assessing the merit of using similar approaches in future implementation efforts [45]. The FE for this project included developmental FE, implementation-focused FE, progress-focused FE, and interpretive evaluation. Summative evaluation will quantitatively assess the effectiveness of the EBQI/F intervention in comparison to sites randomized to the study’s control condition.

### Developmental FE

The objectives of developmental FE are to identify determinants of current practice regarding monitoring/management of metabolic side effects, identify available QI resources, identify barriers/facilitators, and engage clinical stakeholders in defining key issues and potential solutions in addressing project goals. Key staff at intervention and control sites have completed semi-structured telephone interviews, providing their perspectives on these issues. Participants also completed the Organizational Readiness to Change Assessment (ORCA), described below.

### Implementation- and progress-focused FE

The objectives of implementation-focused FE are to document implementation processes and exposure of site participants to the intervention, identify barriers to and deviations from the planned local implementation strategy, and modify the strategy as needed to overcome barriers [45]. The objective of progress-focused FE is to monitor progress in achieving implementation goals and performance targets, enabling the facilitator to modify intervention tools/strategies as needed to maximize potential for success [45]. The facilitator monitors implementation processes and progress through regular contacts with a primary contact at each intervention site. Because the facilitator’s attention to implementation- and progress-focused FE activities will be directed exclusively to EBQI/F sites, a survey of metabolic monitoring and management practices (SMM) will be administered to Mental Health Service Chiefs at all sites prior to the start of the Implementation Phase and at the end of the Sustainability Phase.

### Interpretive evaluation

The objective of interpretive evaluation is to obtain stakeholder perspectives on the perceived value of the EBQI/F intervention, barriers and facilitators encountered, satisfaction with the implementation process, unintended consequences, and any needed refinements. Only intervention sites receive interpretive evaluation.

Stakeholder experiences with the intervention will be assessed after the Implementation Phase through semi-structured qualitative telephone interviews with the two most involved participants in implementation activities at each EBQI/F site. All interviews will be audio-taped and transcribed for qualitative data analyses.

### Summative evaluation

#### Data sources

Summative evaluation data sources include data extracted from VA databases; medical record abstraction; and surveys (SMM and the Organizational Readiness to Change Assessment [ORCA]) administered to the participants. The VA datasets contain patient demographics, inpatient and outpatient encounters and associated diagnoses, pharmacy and laboratory data, and vital signs. Patient data on metabolic side-effect monitoring and management will be collected on all Veterans meeting inclusionary criteria at each site, and these data will be analyzed and presented at the VA facility level.

#### Metabolic side-effect monitoring

Data will be extracted for all patients who were treated at a study site and were prescribed a new antipsychotic medication (defined as a ‘new antipsychotic start’ or the addition of, or switch to, an antipsychotic medication that had not been prescribed in the previous 180 days) [20] and who would be due for monitoring or management of metabolic side effects during any of the three six-month phases of the study. If monitoring of a metabolic parameter (weight, glucose or hemoglobin A1c, and low-density lipoprotein [LDL]) is documented as occurring within the window of 30 days before to 30 days after a new prescription, we defined this as completed ‘baseline’ monitoring. The recommended 90-day ‘follow-up’ monitoring is defined as monitoring of a metabolic parameter between 31 and 120 days following the new prescription date. For each study site, the proportion of patients due for monitoring that received monitoring at each time point for each parameter will be calculated and aggregated for each month in each study phase. All patients whose monitoring window ends within a given month will be included in the denominator to calculate that month’s (baseline or follow-up) monitoring rate.

#### Metabolic side-effect management

Performance of recommended management actions will be assessed for patients with evidence of obesity (BMI ≥30), hyperglycemia (plasma glucose ≥200 mg/dL), elevated hemoglobin A1c (≥6.5), or elevated LDL (≥160 mg/dL) at either the baseline or 90-day follow-up window, or weight gain (>5% gain from baseline) at the 90-day follow-up window. Because VA datasets do not contain a reliable indicator of whether a laboratory test was performed when the patient was in a fasting state, these thresholds for management are set at a higher level than indicated in practice guidelines (*e.g*., 126 mg/dL for glucose). However, diabetes practice guidelines indicate that two random glucose tests with results ≥200 mg/dL may be used to diagnose diabetes [17].

Medical records will be reviewed to better assess initiation of management actions for patients who are found to have abnormal results on any of the metabolic parameters. This will not only allow for confirmation of the accuracy of clinical management actions captured by the electronic datasets, but will also allow for the inclusion of additional information, such as documentation of decision-making regarding antipsychotic choice and of counseling on diet and exercise. Possible management actions and the data source from which they are derived (VA datasets or chart abstractions) are listed in Table 1. Monthly measures of a site’s rate of management for metabolic side effects for these patients will be constructed, combining data from the two sources, using the data abstracted from the medical record as the gold standard.

**Table 1 T1:** Operationalization of measures for guideline-recommended metabolic management

**Parameter**	**Thresholds**	**Management elements**	**Operationalization**	**Data source**
**Weight**	BMI ≥30, weight gain >5%	Antipsychotic management	Switch to medication w/ lower propensity for weight gain	VA dataset
		Lifestyle modification	Counseling on diet, exercise, and behavior modification within 30 days, OR	Chart review
			Nutrition consult within 30 days, OR	VA dataset
			‘MOVE!’ Program encounter(s) within 30 days	VA dataset
		Medication	Orlistat prescription within 30 days	VA dataset
**Glucose**	Plasma glucose ≥200 or Hgb A1c ≥6.5	Antipsychotic management	Switch to medication with lower propensity for elevated glucose	VA dataset
		Lifestyle modification	Counseling on diet, exercise, and behavior modification within 30 days, OR	Chart review
			Nutrition consult within 30 days, OR	VA dataset
			‘MOVE!’ Program encounter(s) within 30 days	VA dataset
		Follow-up	Primary care/diabetes clinic visit within 30 days	VA dataset
		Medication	Hypoglycemic agent within 30 days	VA dataset
**Lipids**	LDL ≥160	Antipsychotic management	Switch to medication w/ lower propensity for elevated lipids	VA dataset
		Lifestyle modification	Counseling on diet, exercise, and behavior modification within 30 days, OR	Chart review
			Nutrition consult within 30 days, OR	VA dataset
			‘MOVE!’ Program encounter(s) within 30 days	VA dataset
		Follow-up	Primary care/medicine visit within 30 days	VA dataset
		Medication	Statin prescription within 30 days	VA dataset

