### Data analysis

Because weight gain is a common antipsychotic side effect that increases risk of diabetes and cardiovascular disease [6,9,11], and overweight/obesity is prevalent in patients with psychotic disorders [10,11], the primary outcome measures for the proposed project will be the extent to which weight/BMI is monitored and to which overweight or obese patients receive a guideline-concordant weight management intervention. At each site, the proportion of patients who receive baseline monitoring, follow-up monitoring, and management of metabolic abnormalities will be measured each month against those who were due for such actions during the same time period. We expect EBQI/F intervention sites to gradually increase performance on monitoring and management measures over time. Therefore, we will conduct a time series analysis of monthly performance, with each site contributing six monthly performance measures in each of the three phases of the study. These analyses will estimate the change in rates of baseline monitoring during the Implementation Phase due to intervention (national quality improvement initiative with and without EBQI/F), and allow comparison of these performance changes between sites receiving EBQI/F and those not. Further, these analyses will allow within-phase changes in monitoring rates to be compared between phases; *e.g*., for EBQI/F sites, is the monitoring performance change during the Implementation Phase different from that during the Sustainability Phase? We will similarly collect, summarize, and analyze data from all patients due for follow-up metabolic monitoring and metabolic management (as defined in Table 1) during the three study phases.

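### The management rate counts only patients whose abnormality was recorded by monitoring, which EBQI/F is meant to increase, so the between-arm comparison for Objective 2 may be distorted by who is counted

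*Protocol article*

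**What the plan says.** All references are to the Protocol article.

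- **Management denominator** (Metabolic side-effect management): "Performance of recommended management actions will be assessed for patients with evidence of obesity", or with glucose, hemoglobin A1c or LDL above set thresholds in the baseline or 90-day window, or with weight gain above 5% at follow-up. Charts are reviewed for "patients who are found to have abnormal results on any of the metabolic parameters", and a monthly "rate of management for metabolic side effects for these patients will be constructed".
- **Data analysis** repeats this in general terms: "management of metabolic abnormalities will be measured each month against those who were due for such actions".
- **Monitoring denominator** (Metabolic side-effect monitoring), by contrast: "All patients whose monitoring window ends within a given month will be included in the denominator". It does not depend on being tested.
- **Intended effect on monitoring.** Objective 1 is to test the effect of EBQI/F on monitoring. Data analysis adds: "We expect EBQI/F intervention sites to gradually increase performance on monitoring and management measures over time". The section EBQI/F intervention describes a computer routine revised to "identify patients who had been prescribed a new antipsychotic medication and were due for baseline or initial follow-up monitoring".
- **Adjustment** (Data collection for and definition of covariates): demographics and pre-existing diagnoses, summarized by site, enter the models.

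**The concern.** Entry to the management denominator requires a measurement made after randomization, and making more of those measurements is a goal of the intervention. If monitoring rises more at EBQI/F sites, patients who would have gone unmeasured under control conditions join the denominator there and not at control sites. Randomization does not protect a rate conditioned on a variable that the intervention changes.

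The article itself gives a reason why newly detected patients could differ. The covariates section says that frequent primary care users are more likely to meet monitoring criteria, and Table 1 counts a primary care visit within 30 days as management for glucose and lipids. One factor can thus drive both entry and success.

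Weight management is one of the two primary outcome measures. A change in its slope could partly reflect who is counted and not how patients are treated.

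**Working it through.** **The yardstick.** The article gives no figure for this effect, so Table 3 supplies the scale. Check of its between-arm row: slope variance per site v = v_b + the generalized least squares slope variance over six months with first-order autocorrelation, and SE = √(2v/6) for six sites per arm. In the expected scenario v = 12.46, so SE = √(2 × 12.46/6) = 2.04. The detectable difference is 2.80 × 2.04 = 5.71 with normal quantiles and 6.34 with a noncentral t on 10 degrees of freedom. The stated 6.1 lies between. The other scenarios behave the same way (4.95 to 5.49 against 5.3; 6.70 to 7.44 against 7.2). Table 3 is not disputed.

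**The selection effect.** Let m0 and m1 be the monitored shares without and with EBQI/F, pA the management rate in patients who would be monitored anyway, and pB the rate in patients detected only because of EBQI/F. With no change in how anyone is managed once detected:

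- apparent rate = [m0·pA + (m1 − m0)·pB] / m1
- shift = [(m1 − m0)/m1] × (pB − pA)

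The shift depends on the difference pB − pA and not on the level of pA.

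**Inputs.** m0 comes from the 32-facility study in Existing VA practice, patterns and outcomes. m1 = m0 + 30.5 points, that is, 6.1 points per month over five steps. This is a detectable difference under expected variance parameters and not an expected effect, so it marks a large gain. Assumptions: pB − pA = −20 points, and abnormality equally common in both groups of patients.

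| Parameter, window | m0 → m1 (%) | Newly detected share | Shift (points) | Per month (÷5) |
|---|---|---|---|---|
| Weight, baseline | 67 → 97.5 | 31.3% | −6.3 | −1.3 |
| Weight, follow-up | 49 → 79.5 | 38.4% | −7.7 | −1.5 |
| Glucose/A1c, baseline | 46 → 76.5 | 39.9% | −8.0 | −1.6 |
| Glucose/A1c, follow-up | 27 → 57.5 | 53.0% | −10.6 | −2.1 |
| LDL, baseline | 32 → 62.5 | 48.8% | −9.8 | −2.0 |
| LDL, follow-up | 16 → 46.5 | 65.6% | −13.1 | −2.6 |

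Example row: 0.305/0.795 = 0.384, and 0.384 × (−20) = −7.7.

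**Range.** If pB − pA = +20 the signs reverse, and if pB = pA every shift is zero. With a monitoring gain of only 10 points the shift is −2.6 (weight baseline), −3.4 (weight follow-up) and −7.7 (LDL follow-up), or about −0.5, −0.7 and −1.5 per month.

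**Can it hide a real gain?** Take follow-up weight with pA = 79% (100% minus the 21% without a recorded weight intervention in the Inspector General report; that report covers a year, so the trial's 30-day measure may be lower) and pB = 59%. A true 5-point gain for everyone gives (0.49 × 0.84 + 0.305 × 0.64)/0.795 = 76.3%, which appears as −2.7 points.

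**The case against.** **The conditional rate answers a legitimate question.** Once an abnormality is known, is it acted on? The study objectives separate monitoring from management, and an all-due rate blurs them. In the follow-up weight example with no true gain, detected-and-managed among all abnormal patients rises from 0.49 × 0.79 = 38.7% to 38.7% + 0.305 × 0.59 = 56.7%, purely because more patients were weighed. This stands. It is partly a choice of estimand, and it is why the conditional rate should be kept.

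**Newly detected patients may be managed equally often.** Further routines list patients with abnormal laboratory results and show whether action followed. This also stands, although as described that list covers laboratory results and not weight.

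**The exposure of weight is limited.** Obesity qualifies a patient in either window, so on the cited rates at least 67% are already measured. This stands for BMI. It does not help the weight-gain criterion, which needs a weight in both windows.

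**There is some adjustment.** Site-level diagnoses give partial control for case mix but do not model entry to the denominator. Phase-specific slopes do not help, because the shift would occur during implementation in one arm. The sensitivity analyses in the Discussion concern lower thresholds and fasting status. Additional file 1 is not shown, but the article already fixes the denominator.

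**Control sites have monitoring tools too.** They have MIAMI Project resources, including a routine for initial monitoring. The Discussion says relatively few providers use them, so a differential rise is plausible but not certain.

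**An all-due denominator is not immune either.** A switch of antipsychotic counts both as a new index prescription and, in Table 1, as a management action. An intervention that prompts switches can add patients to that denominator. The fix has to allow for this.

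**Conclusion.** The between-arm comparison of management rates conditions on a post-randomization variable that EBQI/F is designed to change, and nothing in the article corrects for this or acknowledges it. The comparison may therefore be biased.

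A reader might infer that it is biased, or that it will show harm or benefit that does not exist. The documents do not support that. Bias needs both a larger rise in monitoring at EBQI/F sites and a different chance of management in newly detected patients. The first is the trial's hypothesis. The second is made plausible by the covariates section but is not quantified anywhere.

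Under the assumed 20-point difference and a rise equal to the full detectable slope, the effect is about 1.3 to 1.5 points per month for weight and 1.6 to 2.6 for glucose and LDL. All are below the detectable 6.1, so selection of this size alone would seldom produce a significant result, but it could mask or inflate a moderate true change. Weight, the primary parameter, is the least exposed. This calls for an inexpensive addition to the analysis and does not invalidate the management outcome.

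**What to change.** Keep the conditional rate as the process measure, and state that its between-arm difference is not a purely randomized effect. Beside it, pre-specify the same slope comparison for two further outcomes:

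- **(a)** The proportion of all patients due in the month who had an abnormality found and managed. Count one index prescription per patient, or at least exclude index events created by a management switch. Unmonitored patients count as not managed, so no further charts are needed.
- **(b)** Dataset-recorded weight management in patients with BMI ≥30 or an obesity diagnosis recorded before the index prescription, using the diagnostic codes already planned. Records from before the baseline window opens (30 days before the prescription) are safer, because weighing inside that window is what EBQI/F aims to increase. Time the outcome from a date defined alike in both arms, such as the index prescription.

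Base the Objective 2 conclusion on agreement of the three analyses.

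**Cost.** Analysis-plan wording, derived variables, and possibly a look-back for earlier BMI in the same datasets. Outcome (a) mixes detection with management and can be numerically low. With 42% obese (the Background figure, used as an assumption), monitoring rising from 49% to 79%, and assumed management of 20% and 5%, it moves from 0.42 × 0.49 × 0.20 = 4.1% to 0.42 × (0.49 × 0.20 + 0.30 × 0.05) = 4.7%. With 79% and 59% managed and monitoring rising to 79.5%, it moves from 0.42 × 38.7% = 16.3% to 0.42 × 56.7% = 23.8%. Its power should be checked. Outcome (b) misses counseling documented only in the chart.

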### MIRECC initiative on antipsychotic monitoring improvement project

Following the Atypical Antipsychotic Workgroup report, Mental Health Services funded the MIRECC Initiative on Antipsychotic Monitoring Improvement (MIAMI) Project to broadly disseminate metabolic monitoring and management recommendations along with promising tools, strategies, and technical assistance to support relevant quality improvement efforts. The MIAMI Project team included clinical and research experts in psychopharmacology, SMI, and implementation science, who further operationalized metabolic monitoring and management recommendations. The MIAMI Project included:

1. A national training meeting (May 2010) attended by approximately 100 providers and clinical managers;

2. The MIAMI Project Technical Assistance Center (TAC) to assist providers and clinical managers in developing quality improvement efforts and to provide additional information on MIAMI Project tools/resources; and

3. A VA intranet website (http://vaww.mirecc.va.gov/miamiproject), with links to relevant clinical practice guidelines, educational resources, and weight management resources.

Available MIAMI Project tools include examples of computerized clinical reminders, a poster summarizing monitoring and management recommendations, an automated computer routine to identify patients due for initial metabolic monitoring, and a psychoeducational weight management program [27,28].

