We then excluded sites not involved in research, using the Office of Research & Development’s directory of research programs. From those sites located within the contiguous 48 states with active research programs, we contacted the mental health clinical manager at the 24 sites with the lowest proportions of ‘MOVE!’ Program utilization (range 0% to 0.66%). Three of the 24 sites were excluded because of an active or planned research project to study metabolic monitoring and/or management. Two sites were excluded because they already had primary care clinicians integrated into mental health clinics. Two sites declined to participate, and leaders at three other sites did not respond to repeated requests for participation in the project. Leaders at the remaining 14 sites attended conference calls with the study PI to obtain further information, and each agreed to have their site included in the final site selection pool. Each completed a brief survey, adapted from a VA Clinical Practice Organizational Survey that included questions on provider stress and ability to pursue practice change [34,35]. Survey scores ranged from 16.1 to 74.2 on a 100-point scale, with higher scores indicating higher levels of stress and lower capacity to pursue practice change. Sites were ranked according to survey scores. The 12 sites with the highest scores were invited to participate in the study, and all accepted. We used the ranked list of sites to identify matched pairs with comparable survey scores, and then randomly selected one site from each pair to receive the intervention, using a random number generator tool available at http://www.random.org. The mean survey score of the intervention sites was 48.9 compared to 51.1 for the control sites. Shortly after this matching, two of the sites withdrew from study participation; however, fortunately, the remaining two sites that had not initially been selected for study inclusion agreed to participate. Both of these sites had low scores on the Clinical Practice Organizational Survey, and thus did not affect the distribution of intervention and control sites on this inclusionary variable. Soon after this change, another site withdrew from the study; however, this occurred at about the same time that one of the previous sites that had earlier declined participation was now willing to participate. Both of these sites had been randomized to the intervention arm, and so the newly available site replaced the withdrawn site, resulting again in 12 sites participating in the study: 6 intervention sites and 6 control sites.

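### Charted counselling alone can meet the weight-management primary outcome, so better charting at facilitated sites could inflate the slope difference, and the described sensitivity analyses would not reveal it

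*Protocol article*

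**What the plan says.** The Data analysis section names two primary outcomes. One is weight/BMI monitoring. The other is the extent to which "overweight or obese patients receive a guideline-concordant weight management intervention".

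Table 1 lists the actions that count for weight. The lifestyle element opens with "Counseling on diet, exercise, and behavior modification within 30 days, OR" and continues with a nutrition consult or a MOVE! encounter. Counselling comes from chart review. The other weight actions (nutrition consult, MOVE! encounter, orlistat, switch of antipsychotic) come from VA datasets. The section on metabolic side-effect management says that chart review adds information "such as documentation of decision-making regarding antipsychotic choice and of counseling on diet and exercise". It builds the monthly rate by "combining data from the two sources, using the data abstracted from the medical record as the gold standard".

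The arms differ in the help they get:
- **Both arms** can use the national tools: "Available MIAMI Project tools include examples of computerized clinical reminders". The section on timing of the intervention says that few providers take them up.
- **Intervention sites only** get the design phase with local performance data, external facilitation, and progress monitoring against performance targets (EBQI design phase; Implementation phase; Implementation- and progress-focused FE). Table 2 costs the installation and customization of the computer routines as an EBQI/F activity.

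The sensitivity analyses described in the Discussion concern overweight patients, intermediate glucose and LDL values, and fasting status.

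**The concern.** A counselling note measures what was written down. Facilitation aims to change care, but it may also lead staff to record counselling that they already gave and used to leave unrecorded. If so, the measured rate climbs in one arm, during the Implementation Phase, with no change in care. That is the contrast the random coefficients model tests. Randomization balances charting habits at the start in expectation only. Neither the pre-implementation data nor the patient-mix covariates can remove a charting change that the intervention itself causes.

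At stake is the interpretation of one of the two primary outcomes. A positive slope difference would be reported as more guideline-concordant management, and nothing described in the article would show how much of it rests on notes and how much on coded services or prescriptions. The weight/BMI monitoring outcome is not exposed through this counselling element.

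**Working it through.** **Step 1. The yardstick.** Table 3 gives detectable between-arm slope differences of 5.3, 6.1 and 7.2 points per month (best, expected, worst). To confirm what these figures mean, take the variance of one site's slope over six monthly points as v_b plus an AR(1) residual part, estimated by generalized least squares. This gives 9.36, 12.46 and 17.17. The detectable difference is m × √(2 × variance / 6). With a noncentral t multiplier m = 2.998 (two-sided 0.05, power 0.80, 15 degrees of freedom):

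- best: 2.998 × √(2 × 9.36 / 6) = 5.30
- expected: 2.998 × √(2 × 12.46 / 6) = 6.11
- worst: 2.998 × √(2 × 17.17 / 6) = 7.17

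All three match to rounding. The article does not state the degrees of freedom, and 15 was chosen to fit. A normal multiplier gives 5.71 in the expected scenario, and 10 degrees of freedom give 6.34. So 6.1 is a within-phase slope difference over six monthly values per site.

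**Step 2. A pure charting artefact.** Let a constant share p of eligible patients truly receive counselling. Let the share of that counselling that is charted rise steadily from s0 to s1 at intervention sites only. Six monthly points span five intervals, so

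false slope = 100 × p × (s1 − s0) / 5 points per month.

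The article gives none of p, s0 or s1. All are assumptions.

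| p | s0 to s1 | Total rise (points) | False slope per month | Share of 6.1 |
|---|---|---|---|---|
| 0.5 | 0.5 to 0.7 | 10 | 2.0 | 33% |
| 0.7 | 0.5 to 0.8 | 21 | 4.2 | 69% |
| 0.9 | 0.5 to 0.8 | 27 | 5.4 | 89% |
| 0.7 | 0.4 to 0.9 | 35 | 7.0 | 115% |

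A wider grid (p from 0.3 to 0.9; charting 0.5 to 0.6 up to 0.4 to 0.9) runs from 0.6 to 9.0. Stated directly, a rise in charted counselling from 30% to 50% gives 20 / 5 = 4.0 points per month, or 4.0 / 6.1 = 66%. Dividing by six months would give 3.3, but six monthly values have only five steps.

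**Step 3. What an artefact needs to reach the yardstick alone.** 6.1 × 5 = 30.5 points in the expected scenario. In the best and worst scenarios it is 5.3 × 5 = 26.5 and 7.2 × 5 = 36.0.

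**Step 4. Limits of the formula.** It assumes that no counselled patient already counts through a dataset action; overlap shrinks the false slope. It also assumes a steady rise. An abrupt change would appear partly as a shift in level.

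**The case against.** The strongest reply is that the mechanism is inferred, and this stands. No passage says that facilitation or the tools raise charting. Reminders are offered only as examples, both arms can obtain them, and intervention sites need only consider them. The action-tracking routine is weak evidence. It is meant to "generate a list of patients with abnormal laboratory results, and indicate whether management actions had been taken", which concerns laboratory results, not weight, and the example given is a prescription. The performance data given to sites before the visit came from VA databases, so a counselling note may not have affected them.

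Counselling may also be genuine care that the datasets miss, which is a sound reason to read charts. Chart precedence is not the source of the exposure, because counselling has no dataset entry to override.

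Table 1's ORs work within the lifestyle element. The rule across switch, lifestyle and orlistat is not given, so counselling alone scores a patient as managed only if any listed action suffices.

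A reader might infer that chart text must drive the outcome, because MOVE! use at the 24 candidate sites was at most 0.66% while the Inspector General's report found that only 21% of obese or overweight patients lacked a weight-management record. The documents do not support this. The MOVE! figure follows FY08 prescriptions, before the national training. The other figure covers a different population, and the article does not say whether those records were notes or coded services. Nutrition-consult rates are not given.

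None of this removes the main point. One arm alone gets sustained attention to a target that a note can meet, and no described analysis separates notes from services.

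**Conclusion.** The concern holds as a possible arm-specific ascertainment bias in one primary outcome. It rests on three things the article states: a counselling note is enough for the lifestyle element, it is found only in the chart, and only one arm is facilitated and tracked against targets. It also rests on one inference, that such attention could change documentation.

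The size is unknown. Under the four illustrated assumptions the false slope is about 2 to 7 points per month. Reaching the detectable 6.1 alone would take a charting-driven rise of about 30 points. More often the artefact would inflate a real effect. A reader might go further and conclude that an observed difference would consist wholly of ticked reminders. That is the extreme case, and nothing in the article shows it.

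**What to change.** Keep the composite as the primary outcome. Pre-specify a supportive weight-management rate built only from VA-dataset actions (MOVE! encounter, nutrition consult, orlistat, qualifying switch). Report by arm and phase, with confidence intervals, both this rate and the share of patients who count as managed through charted counselling only.

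If the composite effect is carried by charted counselling alone, state that better documentation cannot be separated from better care. Do not require the two rates to agree in direction. If counselling truly rose and coded services did not change, the sign of the coded estimate across six against six sites would be close to a coin toss, so about half of genuine gains would be mislabelled.

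The cost is one additional analysis of data already being collected. The Trial status section places the study early in implementation, so pre-specification was still feasible when the article was written. The drawback is that the dataset-only rate will probably be low and imprecise. It can qualify the primary result but not replace it.
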